### Quality Assurance and Monitoring

#### Overview

The project manager and research officer will be responsible for the day-to-day administration of the research. They will meet regularly (fortnightly to monthly, depending on the trial needs) with the primary investigator ([name]) to discuss the research progress. Other investigators will attend these meetings as needed, and full team meetings will be conducted several times per year throughout the project. Recruitment of trial sites and tracking of participant numbers will be monitored closely.

#### Follow-Up Interview

In the follow-up survey, participants in the active intervention condition will be asked to indicate their willingness to be interviewed regarding their experience using the program by a member of the research team after the 6-month trial period ends. Interviews will explore experiences using the program and ideas to facilitate implementation. We expect that up to 15 interviews will be required to obtain a breadth of different experiences from participants from different workplaces, work levels (eg, management and employees), ages, and genders on their experiences and views on the co-designed program. Interview participants will be selected based on this diversity. The interview will be recorded on Zoom (Zoom Video Communications, Inc) or audio recorded over the telephone for accuracy, with the audio recording only stored on secure Australian National University (ANU) IT servers. The recordings will be transcribed for analysis by a professional external transcription company. Any references to the participants’ name or workplace will be removed in transcription to reduce the chance of identification in any publications. Consent for participating in interviews, recording of interviews, and using interview data for publication will be obtained separately for the trial. Participants will be emailed an Aus $50 (US $33) e-gift card to remunerate for their time and effort participating in an interview. Participants will receive an e-gift card if they commence the interview, regardless of whether they finish it or not.

### Ethical Considerations

#### Overview

The ethical aspects of this study have been approved by the ANU Human Research Ethics Committee (protocol number 2023/053). Participants will be presented with comprehensive information regarding the study before providing informed consent on the web. Participants will not be provided with compensation for participating in the study.

Ethical issues in the literature relevant to this study relate predominantly to the potential for coercion; the use of internet-based programs; and workplace confidentiality, health, and safety concerns. These concerns include the web-based storage of data, managing privacy of personal information, obtaining consent to participate, providing opportunities to withdraw from the study, and ensuring any distressed participants in the study are provided with appropriate assistance. These issues are addressed in the following sections.

#### Data Availability, Storage, and Privacy

The major ethical issue relates to ensuring the privacy of web-based data collected and stored in password-protected computers and a secure web portal for web-based data collection and delivery of the web-based program. The website that houses the data will be assessed by ANU via a Privacy Impact Assessment to ensure it meets the privacy standards outlined in the Australian Privacy Act. Survey data will be initially stored on the custom-built secure website. After downloading it from this portal, any potentially identifying information (ie, email addresses) will be removed from the main data file and stored in a separate file. These will be linked by an ID code that will not contain any individually identifying information. We will explain to participants this is primarily so that if they wish to withdraw from the study, we can relink their data across the 2 files using this unique code and delete it.

Audio recordings and transcripts for the qualitative interviews will be stored on a secure server with access restricted to the researchers involved in the study and the IT support staff. Their interview and transcript data will be identified by a code we assign them, which will be unique to each participant but contain no identifying details (ie, a number). The audio recordings and transcripts will not be linked with the survey data and will be stored separately from the data we collected from the surveys.

We will protect the privacy of web-based data collected after downloading by storing it on secure university servers with access restricted to authorized personnel only (the project team and IT support staff responsible for managing the server). Any identifiable data associated with this project (eg, contact emails) will be deleted after the first publication is submitted. Following this, deidentified data will be retained and stored in web-based data repositories for data aggregation purposes (eg, meta-analyses) and data sharing.

The information collected from the RCT will be presented as group summaries (in aggregate form) for the purpose of publication in relevant academic journals and conference presentations. Findings will be presented with no reference to individuals. For the interview data, during the publication of results, we expect to refer to individual quotes from participants; these will be identified by broad demographic data (ie, age range, gender, and workplace type or industry only). Furthermore, individual workplaces will not be identified in any publications.

#### Participant Withdrawal and Distress

Participants will be informed that they can withdraw from the study at any time. Participants will only need to contact the researchers to withdraw if they have provided their email. If a participant requests to have their data removed from the study by sending an email to the researchers, the principal investigator ([name]) will action this request. Participants will be able to withdraw from the study at any time until the first publication is submitted, which is expected to be in early 2025. After this, we will be deleting emails and will be unable to identify an individual’s specific data. We will only recruit workplaces that have an EAP to ensure that employees experiencing mental health concerns can access effective and immediate care. We will encourage any participants who are experiencing discomfort to contact their EAP or another crisis service (eg, Lifeline). In addition, given that the purpose of the trial is to encourage help-seeking, the intervention itself will contain explicit encouragement to seek help throughout their participation in the project if they are experiencing any distress. As the program aims to improve help-seeking, our invitation letter to workplaces will clearly outline potential outcomes (such as increased utilization of EAP services) and benefits (such as enhanced mental health awareness among employees) that their participation in the trial may bring to their workplace.

#### Coercion and Informed Consent

Given that the trial will be conducted in workplaces, a critical issue is perceived coercion and pressure to participate in the study, whether explicit or implicit. Therefore, it is essential that it is made clear to the workplace key representatives, who will be coordinating the sending of invitation emails, and to the potential participants, who will be employees of the organizations, that their participation is entirely voluntary. Participants will be informed that those sending invitations to employees (eg, human resource staff and managers) will not have access to the participants’ data. In addition, workplaces will not be able to determine which of their employees have participated in the study, unless the employee wishes to tell them. We will emphasize the voluntary nature of the trial in the information and consent web-based forms for participants and explain this clearly in all communication with the workplace key representatives. Furthermore, we will discuss with each individual workplace their potential involvement in the trial and work collaboratively with them to assist them in meeting any workplace health and safety requirements relevant to participation both before and during the conduct of the trial. In addition, the workplace key representatives will be advised that we will inform our ethics committee (ANU Human Research Ethics Committee) of the details of each workplace recruited for the study to assist them in managing and supporting workplaces if any ethical concerns are raised.

Participants will be provided with a PDF version of the participant information sheet that they can save or print. The informed consent form will be provided through an information web page. The web-based consent process will require participants to answer a question indicating that yes, they wish to consent to participate in the study. Participants who do not consent can close the web page and will not proceed any further.

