#### Randomization

Given the cluster design, we will use a minimization approach to randomization [39]. Minimization is a type of randomization where the first participant (or cluster) is randomized and subsequent selections are allocated in a way that minimizes the imbalance on specific factors between groups. This method is helpful for a design with few participants (or clusters) and has the advantage of making each condition more closely matched on key factors across the trial. To implement this, we will use a preprogrammed computer algorithm that will assign each new workplace recruited into the trial into a condition. This process will aim to balance across conditions on the following key workplace characteristics: (1) workplace type (office-based vs non–office based), (2) organization size (<200 vs >200 employees), and (3) location (Australian Capital Territory or New South Wales or Victoria vs other Australian state or territory). Once a workplace has been allocated a condition, we will discuss with their key representative what participation in the trial involves and provide them with an email or SMS text message (depending on their preferred communication with employees) with an embedded link to their assigned study recruitment website. We expect the text to read as follows:

Would you like to participate in a research study testing a new resource for supporting employee wellbeing? Learn more about your mental health and wellbeing by completing a survey and a brief online program today: <link>.

We will ask the workplaces to send invitations to all their employees themselves, with each workplace determining who from within their organization will send this invitation. This process is designed to increase ecological validity, as the goal for the program is for it to be delivered by workplaces, we expect this to be a minimal burden (ie, 1 or 2 SMS text messages or emails) on the workplace administration staff tasked with sending invitations.

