#### Participant Recruitment and Informed Consent

Participants will be recruited on the web through participating workplaces. To be eligible for the trial, potential participants must fulfill the following criteria:

Be an employee in a participating Australian workplaceBe aged ≥18 years, living in Australia, and fluent in reading and understanding EnglishHave access to a device (eg, desktop, laptop, tablet, or smartphone) and a reliable internet connection

If participants complete the abovementioned screening criteria and are not eligible, they will be informed and provided with a list of relevant help-seeking resources.

After being assigned a condition, the workplace will send a brief email or SMS text message to their employees inviting them to participate in the trial (refer to the Randomization section for an example). The email or SMS text message will contain a link to the web page containing information about the study. Then, the employees who click the link provided by their employers will be taken to the information and consent web-based page, where they will be invited to read the information that the study and provide their consent to participate in the study on the web. This process will be confidential, and their work organization will not be informed of who among their employees has consented to participate in the trial. Participants can complete the preintervention, program, and postintervention survey in a single session. Furthermore, participants can save their progress at the bottom of the screen if they wish and re-enter the survey or program at the last point they left off by reaccessing the link from their email or SMS text message. In addition, they will be sent reminders to complete the program if they have not done so within the expected time frames (Figure 1).

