### Trial Delivery

The trial will be delivered using a custom-designed website that will contain the 2 web-based programs. This website will allow self-report assessments, intervention materials, and email reminders to be delivered seamlessly to the participants. Furthermore, the website will collect and securely house the survey data collected. To streamline access and reduce the need for participants to create log-ins while maintaining security and confidentiality, participants will only need to provide an email to access the program.

If surveys or the program are discontinued, participants will be emailed a single reminder (at 48 hours if they discontinue any part of the preintervention, program, and postintervention survey and 1 week for the 6-month follow-up survey) with a unique link to access the program from their email account to continue from where they left to complete that part of the study. We expect most participants will complete the preintervention, program, and postintervention surveys in one 40-minute sitting. As such, we do not anticipate that these reminders will be needed frequently; however, given that people could discontinue the program or surveys, we have a method to reconnect them with the study.

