### Data Collection

#### Overview

Participants who agree to participate in the trial by clicking the link will be asked to provide an email address and complete a brief 10-minute baseline questionnaire. Following completion of the baseline questionnaire, participants will immediately be given access to the web-based program (approximately 20 minutes), which will be followed immediately by the 10-minute posttest questionnaire survey. The 10-minute follow-up survey link will be sent to participants via email 6 months after completion of their allocated condition.

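### The promise that workplaces cannot find out who took part is not ensured for participants who register a work email address, and those among them who leave the job may miss the 6-month survey

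*Protocol article*

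**What the plan says.** The article makes the confidentiality commitment twice, in different strengths. Participant Recruitment and Informed Consent says that "their work organization will not be informed of who among their employees has consented to participate in the trial", which is a statement about what the study team will do. Coercion and Informed Consent goes further and says what the employer is able to find out: "workplaces will not be able to determine which of their employees have participated in the study, unless the employee wishes to tell them".

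The contact procedure is spread over several sections:

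- **Randomization:** "We will ask the workplaces to send invitations to all their employees themselves", by email or SMS according to how the workplace prefers to reach its staff.
- **Trial Delivery:** the platform is meant to "reduce the need for participants to create log-ins while maintaining security and confidentiality", and "participants will only need to provide an email to access the program".
- **Trial Delivery, on interrupted sessions:** a single reminder is emailed "with a unique link to access the program from their email account to continue from where they left". Participant Recruitment and Informed Consent adds that people can "re-enter the survey or program at the last point they left off by reaccessing the link from their email or SMS text message".
- **Data Collection, Overview:** "The 10-minute follow-up survey link will be sent to participants via email 6 months after completion of their allocated condition". No other contact route is described.

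No section asks for a personal address or advises against a work one.

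**The concern.** The Ethical Considerations overview lists coercion and workplace confidentiality among the main ethical issues of the trial, so employees may rely on this promise when they decide whether to report symptoms and help-seeking. The promise is absolute, but the procedure makes it depend on which mailbox the participant happens to give. Someone who arrives from an employer's email may well enter the same account.

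Two things are at stake. One is that a participant is told something the study cannot guarantee. The other is retention: a work account may no longer be usable once the person leaves the employer, and email is the only stated route to the 6-month survey. Leaving a job may be connected with mental health or work functioning, which are among the outcomes measured at that visit.

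**Working it through.** There is no stated figure to reproduce. The check sets the promise beside the procedure, then finds which data depend on 6-month contact, then gives a scale under assumptions.

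**1. Promise against procedure.**

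- The invitation itself discloses nothing, because it goes to all employees.
- Messages sent after sign-up go only to people who enrolled, so their presence in a mailbox does identify a participant.
- This does not depend on anyone breaking off. A person who completes the program in one sitting is still sent the 6-month link.
- Data Availability, Storage, and Privacy covers the study website (including a privacy impact assessment) and the university servers. It does not reach a message held in an employer-administered mailbox.

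So the narrower statement, that the organization will not be informed, is consistent with the procedure. The stronger statement, that the workplace will be unable to determine participation, holds only if the address is not a work one or the employer does not look. The article imposes neither condition.

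**2. Data that depend on the 6-month link.**

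- The primary end point is posttest, normally reached in the same sitting as baseline, so it is essentially untouched.
- Under Secondary Outcomes, 6 months is the main time point for every secondary outcome except mental health literacy.
- In Table 1, help-seeking behavior, depression, anxiety, distress, work and activity impairment and quality of life are measured only at baseline and 6 months. A participant not reached at 6 months has no post-baseline value on any of these.
- The follow-up adverse-event question and the 6-month cost and QALY inputs come from the same survey.
- Power and Recruitment allows 15% attrition from pre- to postintervention and gives no figure for 6 months.

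**3. Scale, for illustration only.**

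From the article: target 900, attrition 15%, so 900 × 0.85 = 765 at posttest.

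Assumed, not in the article: a share *w* of participants who give a work address, and a share *t* who leave the employer within 6 months, taken as independent. Every such leaver is counted as unreachable.

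Number unreachable for this reason = 765 × *w* × *t*.

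| *w* | *t* | Number | Share of 765 |
|---|---|---|---|
| 0.40 | 0.04 | 765 × 0.016 = 12.2 | 1.6% |
| 0.80 | 0.10 | 765 × 0.080 = 61.2 | 8.0% |
| 0.25 | 0.05 | 765 × 0.0125 = 9.6 | 1.25% |
| 1.00 | 0.15 | 765 × 0.150 = 114.8 | 15.0% |

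The first two rows give the working range of about 12 to 61. The last two show how far it moves under wider assumptions (about 10 to 115).

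As a plain loss of numbers this is modest. Ignoring clustering, losing 8% widens a standard error by a factor of 1/√0.92 = 1.04. The larger worry is that the loss could be selective.

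**The case against.** The strongest reply is that the use of work accounts is inferred from silence. The article never says that they are accepted or expected. Advice on which address to give could sit on the sign-up screen or in the participant information sheet, neither of which is shown, and an article may leave such detail out. This stands as far as it goes: if the instruction exists, the sponsor can cite it and most of the point closes. It does not remove the point, because the objection is to an unconditional statement in the article set against mechanics in the same article.

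Four stronger readings are tempting, and the documents do not support them.

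- **That the promise is broken.** Disclosure needs a work address, employer access to that mailbox, and someone looking. The article establishes none of these, and workplaces using SMS or with non-office staff may produce fewer work addresses.
- **That an employer could read a participant's answers through the link.** The article says only that the session continues from where it stopped. It does not say that earlier answers are shown, it asserts that security is maintained, and it expects reminders to be needed infrequently.
- **That job leavers in general are lost.** Leavers who gave a personal address remain reachable, and nothing excludes them from follow-up.
- **That the missing-at-random assumption fails.** The article gives no evidence that loss by this route depends on unobserved outcomes. Baseline values are collected, and the mixed models use all available data, so dependence on observed baseline severity is compatible with the assumption.

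**Conclusion.** The point holds in limited form. The statement in Coercion and Informed Consent is more absolute than the described procedure can ensure, specifically for participants who register a work address. Those among them who leave the job may not receive the 6-month link.

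The posttest primary comparison is essentially unaffected. Exposed are the 6-month secondary outcomes, the 6-month adverse-event question and the economic analysis. The size of the loss cannot be derived from the documents. The range of about 12 to 61 of 765 rests wholly on the assumed 40-80% and 4-10%, and on treating every leaver with a work address as unreachable. Selective loss is a possibility to guard against, not something shown. This is an inexpensive improvement that is worth making, not a threat to the trial's main conclusion.

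**What to change.** In Trial Delivery and in the Data Collection overview, state that participants are asked at sign-up for a personal, non-work email address. Have the website warn and ask for an alternative when a work domain is entered. Send reminders and the 6-month link from a neutral sender with a neutral subject line.

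Where a work address is still given, qualify the sentence in Coercion and Informed Consent and the information sheet. Suggested wording: *The study will not tell your workplace whether you took part, but it cannot control who has access to a work mailbox.*

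The cost is one line of sign-up text, a domain check on a website that is already custom-built, and a wording change in the participant information. The downside is small: a few people may decline to give a personal address or may mistype it.

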#### Work Health and Safety Regulations

We will engage in discussions with key representatives from workplaces regarding their potential participation in the trial. During these discussions, we will address any relevant Work Health and Safety regulations that may apply, which we will bring up when we approach workplaces to gauge their interest in participating in the trial. Furthermore, we will provide ongoing support to workplaces in navigating any potential Work Health and Safety regulation issues relevant to the trial while it is being conducted. Our letter to the key representatives in potential workplaces will explain that we will provide this support but that workplace’s will to seek their own advice on workplace health and safety requirements, as well as what may happen because of their workplace’s participation (eg, a potential increase in those seeking help from EAP services).

